# Best-BRA (Is subpectoral or prepectoral implant placement best in immediate breast reconstruction?): a protocol for a pilot randomised controlled trial of subpectoral versus prepectoral immediate implant-based breast reconstruction in women following mastectomy

**DOI:** 10.1136/bmjopen-2021-050886

**Published:** 2021-11-30

**Keywords:** breast surgery, breast tumours, plastic & reconstructive surgery, qualitative research

## Abstract

**Background:**

Implant-based breast reconstruction (IBBR) is the most commonly performed reconstructive procedure following mastectomy. IBBR techniques are evolving rapidly, with mesh-assisted subpectoral reconstruction becoming the standard of care and more recently, prepectoral techniques being introduced. These muscle-sparing techniques may reduce postoperative pain, avoid implant animation and improve cosmetic outcomes and have been widely adopted into practice. Although small observational studies have failed to demonstrate any differences in the clinical or patient-reported outcomes of prepectoral or subpectoral reconstruction, high-quality comparative evidence of clinical or cost-effectiveness is lacking. A well-designed, adequately powered randomised controlled trial (RCT) is needed to compare the techniques, but breast reconstruction RCTs are challenging. We, therefore, aim to undertake an external pilot RCT (Best-BRA) with an embedded QuinteT Recruitment Intervention (QRI) to determine the feasibility of undertaking a trial comparing prepectoral and subpectoral techniques.

**Methods and analysis:**

Best-BRA is a pragmatic, two-arm, external pilot RCT with an embedded QRI and economic scoping for resource use. Women who require a mastectomy for either breast cancer or risk reduction, elect to have an IBBR and are considered suitable for both prepectoral and subpectoral reconstruction will be recruited and randomised 1:1 between the techniques.

The QRI will be implemented in two phases: phase 1, in which sources of recruitment difficulties are rapidly investigated to inform the delivery in phase 2 of tailored interventions to optimise recruitment of patients.

Primary outcomes will be (1) recruitment of patients, (2) adherence to trial allocation and (3) outcome completion rates. Outcomes will be reviewed at 12 months to determine the feasibility of a definitive trial.

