#### Recruitment

Participants will be recruited and randomised over a 12–18 month period by surgeons and research teams working together at participating centres. All female patients undergoing mastectomy who elect to have an IBBR will form the target population. Research teams at each site will maintain a trial screening log following the Screened, Eligible, Approached, Randomised(SEAR) framework^57^ to determine the proportion of:

1. Patients considered eligible for the study (with reasons for non-eligibility).

2. Eligible patients approached about the study (with reasons for not being approached).

3. Eligible patients randomised (with reasons for not being randomised).

4. Randomised patients who receive their allocated treatment (with reasons for not receiving allocated treatments).

The screening log will be reviewed monthly to provide feedback to recruiters and aid understanding of surgeons’ and patients’ preferences for types of surgery as part of the QRI.

Potential participants who will have a mastectomy for breast cancer or risk reduction will be identified from breast cancer and oncoplastic multidisciplinary team meetings (figure 1). The study will be introduced by the treating surgeon when reconstructive options are discussed, and patients will be given written information outlining the study (online supplemental appendix 1). As a key objective of the study is to understand recruitment challenges, these initial consultations will be recorded with patient consent.

10.1136/bmjopen-2021-050886.supp1Supplementary data

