#### Exclusion criteria

Patients will be excluded from the trial if they meet any of the following criteria:

They have delayed reconstruction.They are having revision breast reconstruction surgery.

Patients who smoke, have high body mass index or have had previous radiotherapy to the breast will not be excluded for participation in the trial but surgeons will be encouraged to offer mesh-assisted IBBR in line with updated joint Association of Breast Surgery and British Association of Plastic, Reconstructive and Aesthetic Surgeons’ guidelines for the use of mesh in reconstructive procedures.

Participants will be randomised by the local research team after eligibility and consent have been confirmed at the final clinic visit by the treating surgeon prior to admission for surgery. The randomisation sequence will be generated by a statistician independent of participant recruitment using the random number generator in Stata statistical software (V.16, StataCorp, 2019). Patients will be randomly allocated to the techniques in a 1:1 ratio to either subpectoral or prepectoral immediate IBBR stratified by hospital. Women undergoing bilateral surgery will receive the same procedure on both sides. Allocation will be concealed until the patient has been logged into the system and a study identification (ID) number generated so ensuring that judgements about eligibility are made without knowledge of the next allocation.

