### Outcome measures

In the definitive trial, the proposed primary outcome will be women’s satisfaction with the cosmetic outcome of their reconstruction at 12 months following surgery assessed using the ‘Satisfaction with Breasts’ domain of the validated BREAST-Q questionnaire.^62^ On this basis, for the main trial, 100 patients will be required in each group to allow a true 0.5 SD difference in the BREAST-Q Satisfaction with Breasts domain scale to be detected at 5% significance and 90% power, assuming more than 85% of participants complete the questionnaire 12 months following surgery.

The purpose of this study is to determine the feasibility of conducting a future main trial, specifically whether it will be possible to recruit and randomise 200 patients undergoing IBBR and to collect the required data for the main trial.

The primary outcomes for the Best-BRA study are therefore

1. Recruitment (number of sites recruiting; proportion of eligible women approached that are randomised, women recruited per site per month).

2. Adherence to trial allocation.

3. Outcome completion rates at 3 and 12 months.

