### Sample size calculation

A formal sample size calculation is not required for this external pilot study. At 12–18 months, the number of sites recruiting; proportion of eligible women that are approached and randomised; the number of women recruited per site per month will be reviewed and adherence to trial allocation will be reviewed. There are no plans to assess the feasibility of recruitment and randomisation in any specific patient subgroups. If the study has opened and is successfully recruiting at an acceptable number of sites with high adherence to treatment allocation and follow-up rates, a main trial will be considered feasible and parameters for the full study determined.

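### The feasibility review is timed alongside recruitment, so the 12-month half of the outcome-completion primary outcome will be largely unknown when the feasibility rule is applied

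*Protocol article*

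**What the plan says.** All references are to the protocol article.

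- **Abstract, Methods and analysis.** After naming recruitment, adherence and outcome completion as primary outcomes, it states: "Outcomes will be reviewed at 12 months to determine the feasibility of a definitive trial".
- **Outcome measures.** The third primary outcome is "Outcome completion rates at 3 and 12 months". The intended primary outcome of the definitive trial is "women’s satisfaction with the cosmetic outcome of their reconstruction at 12 months following surgery", and its 100 per group assumes that more than 85% complete that questionnaire.
- **Recruitment.** "Participants will be recruited and randomised over a 12–18 month period".
- **Sample size calculation.** The dated review begins "At 12–18 months, the number of sites recruiting; proportion of eligible women that are approached and randomised" and goes on to women recruited per site per month and adherence. Outcome completion is not in this list. The feasibility rule that closes the section does use it: "successfully recruiting at an acceptable number of sites with high adherence to treatment allocation and follow-up rates, a main trial will be considered feasible".
- **Exclusion criteria (allocation text).** Randomisation follows confirmation of eligibility and consent "at the final clinic visit by the treating surgeon prior to admission for surgery", so the 12 months after surgery start later than randomisation.
- **Data collection.** Reminders for the 3- and 12-month questionnaires run for up to four weeks.

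**The concern.** The review falls at or before the end of recruitment, yet one quantity it is meant to judge takes a further year per woman to observe. The article names no later feasibility review and does not restrict the follow-up criterion to 3-month data.

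The 12-month completion rate is a design parameter of the definitive trial, since it takes the requirement from 85 to 100 per group. Part of the pilot's stated purpose is to find out whether the main trial's data can be collected, and full-study parameters are to be set once feasibility is accepted. If the rule is applied on the stated timetable, that parameter is carried forward either untested or tested only on women recruited first, probably at the first sites to open.

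**Working it through.** **1. Reproduce the plan's own figure.** Inputs: difference 0.5 SD, 5% significance (two-sided assumed), 90% power, 85% completion.

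n per group = 2 × (1.960 + 1.282)² / 0.5² = 84.1, rounded up to 85 (85.03 with the t distribution). Then 85 / 0.85 = 100. The stated 100 per group is reproduced, and it depends on the 12-month completion figure.

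**2. Share of women whose 12-month completion is known at review.** Let R be the recruitment length, T the review time in months from first randomisation, and L the lag (wait from randomisation to surgery plus reminder period).

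- Uniform accrual: share = max(0, T − 12 − L) / R
- Accrual rising linearly as sites open: the square of that ratio

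R and T come from the article, as does the four-week reminder period (0.92 month). The wait for surgery and the accrual shape are assumptions. Three lags are shown: 0; 1.92 (1-month wait plus reminders); and 3 (2-month wait plus reminders rounded to 1 month).

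| Recruitment R, review T | Lag L | Uniform | Rising |
|---|---|---|---|
| R = 12, T = 12 | any | 0% | 0% |
| R = 15, T = 15 | 0 | 3/15 = 20% | 4% |
| R = 15, T = 15 | 1.92 | 1.08/15 = 7% | 0.5% |
| R = 18, T = 18 | 0 | 6/18 = 33% | 11% |
| R = 18, T = 18 | 1.92 | 4.08/18 = 23% | 5% |
| R = 18, T = 18 | 3 | 3/18 = 17% | 3% |
| R = 12, T = 18 | 0 | 6/12 = 50% | 25% |
| R = 12, T = 18 | 1.92 | 4.08/12 = 34% | 12% |
| R = 12, T = 18 | 3 | 3/12 = 25% | 6% |

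The last three rows are the favourable case: recruitment closes at its earliest stated point and the review is held at its latest.

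**3. What is available instead: 3-month completion.** Uniform share = (T − 3 − L) / R, capped at 1.

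- R = T = 18: 15/18 = 83% (L = 0), 13.08/18 = 73% (L = 1.92), 12/18 = 67% (L = 3). Rising accrual gives 69%, 53% and 44%.
- R = T = 12: 9/12 = 75% (L = 0), 7.08/12 = 59% (L = 1.92). Rising accrual gives 56% and 35%.

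**4. When 12-month completion would be mature.** R + 12 + L: about month 24–26 if R = 12 and about month 30–32 if R = 18 (L from 0 to about 1.9). Counted from the last operation, it is 12 months plus four weeks, or about 13 months.

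**5. Precision, as an illustration.** The article gives no pilot target. If 60 women were recruited (assumption), one third due would be 20. With 17 of 20 complete (85%), the Wilson 95% interval is 64% to 95%. With all 60 followed and 51 complete (85%), it is 74% to 92%.

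**The case against.** The strongest reply is that the article does not actually set a dated test on 12-month completion. The list of items for the 12–18 month review covers recruitment and adherence only. Follow-up rates appear in the next sentence, which carries no date and does not say which time point is meant. The abstract's 12 months has no stated origin and could mean 12 months of follow-up for each woman, which would remove the conflict there. The article also declares that it seeks a rapid decision and describes the pilot's scope as recruitment feasibility.

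This stands in part. A reader might infer that a go/no-go test on 12-month completion is fixed for month 12; the text does not go that far. But the per-woman reading rescues only the abstract, because the methods review concerns sites and monthly recruitment over the recruitment span itself. The rule still requires high follow-up rates, and completion at 12 months is still a primary outcome.

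A reader might also infer that the decision would be taken with no follow-up evidence. That is not so: 3-month completion uses the same questionnaire, electronic platform and reminders, and at month 18 it is due for most women under uniform accrual. It is a useful proxy, but it does not measure 12-month completion.

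A third inference, that women not yet due would be counted as failures or dropped to flatter the rate, has no support. The article proposes neither denominator, and that detail commonly sits in the analysis plan.

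Finally, the consequence is bounded. With 100 randomised per group, 75% completion leaves 75 per group and about 86% power; 65% leaves 65 and about 81%. Follow-up continues to 12 months in any case, so the data will exist later. The wide interval also owes something to pilot size, as the 51/60 example shows.

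**Conclusion.** The point holds as a timing mismatch that should be fixed. If the review clock starts at trial opening, 12-month completion is known for nobody at month 12, whatever the accrual pattern. At month 18 it is known for a minority under most assumptions and for at most half in the most favourable case, always the earliest recruits. The assumption of more than 85% completion therefore cannot be adequately checked when the rule "high adherence to treatment allocation and follow-up rates, a main trial will be considered feasible" is applied.

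The month-12 result needs only the clock-origin assumption. The month-18 percentages also depend on the assumed accrual shape and wait for surgery.

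The effect is confined to the 12-month half of one of three primary outcomes. Recruitment, adherence and much of 3-month completion can be judged on the stated timetable. It would be wrong to conclude that the pilot or its descriptive analyses are invalid, since the data are still collected and the power cost of a wrong completion figure is moderate.

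**What to change.** 1. State when the review clock starts (for example, first site open or first woman randomised) and use the same timing in the abstract and the Sample size calculation section.
2. Base the 12–18 month decision on recruitment, adherence and 3-month completion, the last among randomised women whose due date plus the four-week reminder period has passed.
3. Call a go decision at that point provisional. Confirm the follow-up criterion, and the attrition figure used for the main trial, once 12-month completion is mature.

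The text changes are small, but the third step adds a second formal decision point. Final confirmation comes about 13 months after the last operation. Preparation of the main trial can proceed meanwhile on the provisional decision, so the rapid answer on recruitment is kept.

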**Ethics and dissemination:**

The study has been approved by the National Health Service (NHS) Wales REC 6 (20/WA/0338). Findings will be presented at conferences and in peer-reviewed journals.

**Trial registration number:**

ISRCTN10081873.

Strengths and limitations of this studyThis external pilot randomised controlled trial (RCT) with an embedded QuinteT Recruitment Intervention will determine whether it is possible to recruit and randomise patients to a pragmatic trial comparing prepectoral and subpectoral approaches for implant-based breast reconstruction.The QuinteT Recruitment Intervention will allow recruitment challenges to be identified, understood and addressed in real time, allowing a rapid decision about the feasibility of a definitive trial.The external pilot RCT will only address the feasibility of recruitment within an implant reconstruction study; a full-scale main study will still be necessary to compare the clinical and cost-effectiveness of prepectoral and subpectoral implant-based breast reconstruction.

## Introduction

Fifty-five thousand women per year in the UK are diagnosed with breast cancer^1^ of whom 40% will require a mastectomy.^2^ The loss of a breast may dramatically impact women’s quality of life^3^ and in the UK, the National Institute for Health and Care Excellence recommends offering breast reconstruction to improve outcomes.^4^

Implant-based breast reconstruction (IBBR) is the most commonly performed breast reconstruction procedure in the UK accounting for almost 70% of all immediate reconstructions performed following mastectomy.^5^ The introduction of biological or synthetic mesh over the last 10 years has had a major impact on the practice of IBBR. Initially, mesh was sutured between the lower border of the pectoralis muscle and the chest wall extending the subpectoral pocket.^6^ This allowed a definitive fixed-volume implant to be placed under the muscle at the time of surgery, avoiding the need for tissue expansion and a second procedure and resulting in better cosmetic outcomes through improved lower pole projection.^7–14^ There are, however, limited data to support the safety or effectiveness of mesh-assisted subpectoral techniques.^15–19^ The lack of high-quality evidence to support practice is highlighted in the recently updated UK mesh-assisted breast reconstruction guidelines^20^ and in March 2021, the United States Food and Drug Administration issued a Safety Communication stating that acellular dermal matrices, the most commonly used form of biological mesh, are not licenced for use in breast reconstruction and recommended careful discussion of the risks and benefits of mesh with women considering surgery.^21^ Despite this mesh-assisted procedures have become established as the standard of care in the UK, with two-thirds of the 2108 patients undergoing IBBR between 2014 and 2016 in the UK iBRA multicentre prospective cohort study having mesh.^18^ More recently, prepectoral techniques have been introduced in which the implant, fully or partially wrapped in mesh, is placed on top of rather than under the pectoralis major muscle.^22^ These ‘muscle-sparing’ techniques may be less painful and avoid the potentially distressing implant ‘animation’ seen when the pectoralis muscle contracts.^23^

Due to the perceived advantages of the procedure, prepectoral reconstruction is being widely adopted into practice without high-quality evidence to support its use. Early results are promising,^24–31^ but caution is required as subcutaneous implant reconstruction without mesh was previously abandoned by the reconstructive community due to high complication rates.^32–35^ Few studies have directly compared the outcomes of prepectoral and subpectoral mesh-assisted techniques.^18 36–40^ These are small, often single centre studies with limited follow-up, but have demonstrated no differences in short-term clinical^36–39^ or patient-reported^37^ outcomes between prepectoral and subpectoral implant placement. The iBRA prospective multicentre cohort study demonstrated that the short-term complications of prepectoral and subpectoral reconstruction were equivalent^18^ but suggested that at 18 months, satisfaction with outcome, assessed using the validated BREAST-Q, may be greater in patients receiving prepectoral compared with subpectoral techniques.^19^ Caution is required, however as the numbers of patients undergoing prepectoral reconstruction in the iBRA study were small.

High-quality evidence is lacking and there is therefore a need for a well-designed, adequately powered randomised controlled trial (RCT) to evaluate the clinical and cost-effectiveness of IBBR techniques. RCTs in breast reconstruction however are challenging due to patient^41^ and surgeon preference^42^ and expert opinion suggesting that RCTs in breast reconstruction would be ‘unethical’, ‘impractical’ and/or ‘inappropriate’.^3 43–46^ Previous trials in breast reconstruction have been unsuccessful due to failure to recruit.^41 47^ Careful feasibility work to inform the design and conduct of a future study is therefore required before a definitive trial can be planned.

The UK iBRA study^48^ used mixed methods including a national practice questionnaire,^49 50^ a randomisation acceptability survey^51^ and semistructured interviews^52^ with key stakeholders to explore the most appropriate design for a future RCT. This work suggested that a well-designed trial would be feasible and that key areas of uncertainty included the use of biological versus synthetic mesh and prepectoral versus subpectoral implant positioning.^51^ Prepectoral techniques, however, only emerged during the iBRA study and have gained popularity since with two-thirds of survey respondents now offering the technique. Ongoing work in the Pre-BRA study, an IDEAL 2a/2b study evaluating the safety and stability of prepectoral reconstruction prior to definitive evaluation suggests that the technique is safe and sufficiently stable for evaluation in a clinical trial.^53^

While the majority of respondents felt that an appropriately designed RCT in IBBR may be possible,^51^ qualitative interviews with key stakeholders identified a number of barriers to the successful conduct of a future trial.^52^ These included limited understanding of a pragmatic study design and the role of randomisation in minimising bias, issues around clinician equipoise and aspects of surgical culture not being supportive of RCTs.

Although the iBRA study addressed many of the feasibility issues relating to a future trial including the most appropriate comparators, it did not include a randomised study. It is therefore not clear whether surgeons will recruit patients to an RCT comparing two approaches to IBBR or whether patients will consent to be randomised and agree to receive their allocated treatment. Further feasibility work is therefore needed.

We therefore aimed to undertake an external pilot RCT (Best-BRA study- is subpectoral or prepectoral implant placement Best in immediate BReAst reconstruction?). In anticipation of recruitment challenges a QuinteT Recruitment Intervention (QRI)—a complex intervention that aims to rapidly identify, understand and address sources of recruitment difficulties^54^—has been embedded in the study protocol. Having previously been applied to over 60 RCTs to date, the QRI has led to insights about recruitment issues and the development of targeted strategies that have facilitated successful completion of surgical trials that had previously been considered impossible.^54 55^

The Best-BRA study will determine whether it is possible to recruit and randomise women to a study comparing prepectoral and subpectoral IBBR and determine the feasibility of progression to a definitive large-scale pragmatic trial.

## Methods

This protocol adheres to the Standard Protocol Items for Randomised Trials^56^ guidelines.

### Study design

The study will consist of a pragmatic multicentre external pilot RCT with an embedded QRI to determine the feasibility of recruitment and randomisation to either a subpectoral or prepectoral implant reconstruction following mastectomy.

